**4.3. Description of Assessments Performed During the Research**

A motor function assessment will be carried out at the CMPRE at the beginning of the study and 3, 6, and 12 months later to evaluate the effect of the treatment. This assessment includes clinical evaluations and an instrumental evaluation of walking and standing.

**4.3.1. Clinical Assessments**

Several clinical assessments will be performed by a physical therapist:

**Neuro-orthopedic evaluation** A therapist will perform a neuro-orthopedic evaluation of the lower and upper limbs. This examination consists of measuring, (i) using a goniometer, the ranges of motion of the main joints in one or more planes, (ii) the muscle strength of the major muscle groups by asking the subject to move a joint against resistance, and (iii) the spasticity of the main muscles, by moving a joint at a slow then a fast speed to elicit a stretch reflex. This evaluation lasts about 45 minutes.

**GMFM-66-IS** The Gross Motor Function Measure 66 (GMFM-66) is a standardized clinical score with 66 items that assesses the gross motor function and its evolution over time in children with cerebral palsy (45). The GMFM-66-IS is a faster (about 20 to 30 minutes versus 60 to 80 minutes) and validated scoring method for the GMFM-66, using 15 to 39 items (41,46).

**The Early Clinical Assessment of Balance (ECAB)** This is a 13-item clinical scale that assesses postural stability (balance ability) in children with cerebral palsy, with two subscales: one dedicated to head and trunk postural control, and one dedicated to sitting and standing postural control. This scale is validated for children from 1.5 to 11 years old, regardless of the GMFCS level (40,47). The optimal score is 100. The administration of this scale takes about 15 minutes.

**Gross Motor Function Classification System (GMFCS) - Family Report Questionnaire** This questionnaire for parents, based on the child's voluntary movements for sitting, transfers, and mobility, helps to classify the severity of the child's cerebral palsy into one of 5 levels. The questionnaire takes about 2 minutes to complete.

**"Reaching Hand" Questionnaire** This is a questionnaire for parents to assess the abilities of the upper limb and hand in different functional situations for their child with CP (2023 Ma). This questionnaire, validated for children with CP from the age of 2, will assess the expected improvement in hand and upper limb functions related to RAIT. The questionnaire takes about 15 minutes to complete.

**4.3.2. Instrumental Analysis of Gait and Standing**

The Zeno gait analysis walkway (Figure 2) is a mat made of pressure sensors that collects spatio-temporal gait parameters and the progression of foot pressure patterns. These parameters are commonly used to analyze locomotion, identify gait disorders, and evaluate the effect of therapeutic interventions. The patient is asked to walk back and forth on the walkway.

Four inertial measurement units (**Figure 6**) will be used in addition to the walkway, placed on the skin with a double-sided hypoallergenic adhesive: one on the sternum, one over the 5th lumbar vertebra (L5), and one on each foot. This will allow for the measurement, at the beginning of the stance phase, of the peak decelerations of the upper part of the trunk (sternum) and the lower part of the trunk near the center of mass (L5), and to measure the transverse orientation of the feet during walking.

[figure not shown]

**Figure 6:** Example of the mTest3 inertial measurement units (mHealth Technology) used.

Two video cameras, one in profile and one from the front, will allow for the analysis of gait kinematics using the Edinburgh Visual Gait Score, which is validated for children with cerebral palsy (42). The analysis of walking at a self-selected speed, carried out in about 10 minutes, will allow us to collect the following variables:

- **The peak anterior deceleration of the sternum at the beginning of the stance phase** (the first 25% of the gait cycle), which we have shown to be reduced after RAIT in children with CP aged 5 to 12 years (24), will constitute the primary endpoint.
- **The peak downward deceleration of L5 at the beginning of the stance phase**, which we have shown to be reduced after RAIT in children with CP aged 5 to 12 years (24), complements the primary variable for the dynamic behavior of the trunk during walking.
- **The enhanced Gait Variability Index (eGVI)**, recently published, is a composite score based on 9 spatio-temporal parameters that quantifies the distance between the amount of variability observed in an asymptomatic reference group and the amount of variability observed in the patient (38,39). This index assesses instability during walking and the risk of falling. It is usually high in children with CP (48,49).
- **The step width** (between the 2 feet), which is high in children with CP, is one of the strategies to reduce the risk of falling in case of unstable walking (50).
- **The anterior foot load during the 1st double support phase** is a variable obtained on a pressure-sensitive walkway, defined by the ratio between the integrated pressure of the anterior half-foot and the integrated pressure of the entire foot during the 1st double support phase. This variable will be higher when the foot makes contact with the ground on the forefoot, as in children with CP, and lower when the foot makes contact on the heel, as in TD children. This variable, developed for this study, is related to the early anterior displacement of the center of pressure frequently observed in children with CP (51).
- **The Edinburgh Visual Gait Score** (Read 2003) is a score developed for children with cerebral palsy, assessing the extent of kinematic deviations compared to typically developing children.

The analysis of standing will be performed by asking the child to stand still for 30 seconds, 3 times. The analysis of the displacement of the inertial measurement unit placed at L5 using the mSway software from mHealth will allow for the estimation of the mean velocity and the 95% confidence ellipse of the area of horizontal displacement of the body's center of mass (ref).

**4.4. Expected Results**

**For children with CP compared to TD children, it is expected**:

- A higher value for the peak forward deceleration of the sternum and downward deceleration of L5 at the beginning of the stance phase.
- Higher values for step width and the eGVI.
- A greater anterior foot load during the 1st double-support phase.
- Higher values for the mean velocity and area of displacement of the center of mass.
- A higher value for the Edinburgh Visual Gait Score.
- Lower scores on the ECPE, the GMFM-66-IS, and the "Reaching Hand" questionnaire.

**In children with CP, the expected effect after RAIT is an improvement in the endpoints**:

- Decrease in the peak forward deceleration of the sternum and downward deceleration of L5 at the beginning of the stance phase.
- Decrease in step width, the eGVI, and the anterior foot load during the 1st double-support phase.
- Decrease in the Edinburgh Visual Gait Score.
- Decrease in the mean velocity and area of displacement of the center of mass.
- Increase in the scores of the ECPE, the GMFM-66-IS, and the "Reaching Hand" questionnaire.

**4.5. Statistical Analysis Plan**

Statistical analyses will be performed using general linear models, as the overall sample size (N=64) and the size of each group (n=32) are considered sufficient for applying such procedures. The conditions for using these tests will be verified beforehand, particularly the normal distribution of residuals (using quantile-quantile plots and Shapiro-Wilk tests) and the homogeneity of variance (Levene's tests). If the data do not meet these conditions, non-parametric equivalents will be used.

In the first phase, the group effect (Children with CP vs. TD Children) will be analyzed using multivariate analysis of variance (MANOVA) procedures on the dependent kinematic (step width), dynamic (sternum and L5 decelerations and anterior foot position during the 1st double-support phase), and clinical (ECAB, GMFM-66-IS, and "Reaching Hand" questionnaire) variables. A multiple linear regression analysis will also be performed, with the anterior foot position during the 1st double-support phase as the dependent variable and the sternum and L5 decelerations at the beginning of the stance phase as the regressors.

Furthermore, the effects of the specific rehabilitation (2 Groups x 4 Periods) will be tested using the same type of multivariate procedures (MANOVA) and a 2 Groups [PC1 vs. PC2] × 4 Periods [M0, M3, M6, M12] mixed design, with a particular focus on the Group × Period interaction. If this interaction is significant, the analysis of local comparisons using post-hoc procedures (Tukey's tests) will allow us to examine: 1) the significance of the rehabilitation (significant difference between the two groups at M3 with a reduction in the peak sternum deceleration at the beginning of the stance phase for the group that underwent RAIT between M0 and M3); 2) the reproducibility of the RAIT effect (similar differences between M3 and M6 for the RH-RAIT group and between M0 and M3 for the RAIT-RAIT group); and 3) the enhancement of the RAIT effect when it is continued (between M6 and M0 versus between M3 and M0, and between M12 and M0 versus between M6 and M0 for the RAIT-RAIT group; and between M12 and M3 versus between M6 and M3 for the RH-RAIT group).

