**3.2.3. Sample Size Calculation**

The calculation of the number of subjects needed is based on the primary endpoint. The distribution of the peak sternum deceleration at the beginning of the stance phase was Gaussian in our previous study. On average, this distribution was centered on 3.0 ± 1.1 m.s-2 (mean ± 1 standard deviation) in children with CP and on 1.1 ± 0.3 m.s-2 in TD children (24). The expected effect of RAIT is a minimum reduction in the peak sternum deceleration at the beginning of the stance phase of one-third of its value, similar to the effect of RAIT in the previous study (24). To demonstrate an effect of RAIT using a repeated measures ANOVA in which we expect a small effect size, with an alpha level set at 0.05 and a power of 80%, a total sample size of 24 patients, i.e., 12 per group, is necessary (calculation performed using G*Power 3.1 software; **Figure 3).** We expect greater variability in dynamic gait variables (expected in children aged 18 months to 5 years and 6 months compared to children aged 5 to 12 years). Therefore, we plan to recruit 32 children with CP (16 per group), to account for this greater variability and to compensate for potential dropouts.

[figure not shown]

**Figure 3:** Calculation of the number of subjects needed, performed using G*Power 3.1 software.

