**4.6. Study Withdrawal and Stopping Criteria**

The parents of the participating child are free to withdraw their child from the study at any time without needing to provide a reason. The protocol will also be terminated if a socio-medical imperative arises during the study that requires it to be stopped. In such a situation, the final assessment will be performed at the time of study discontinuation, if possible. The study will be stopped after the last visit of the last enrolled patient. The sponsor can decide to terminate the study prematurely. The sponsor must then inform the CPP within 15 days and state the reasons for this decision. At the end of the study, the sponsor will inform the CPP and the investigating centers within 90 days. In the event of premature study termination, the investigators must promptly inform the participating patients and ensure they receive appropriate follow-up care.

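### Section 4.5 justifies its models with N=64 and 32 per group, but the randomised comparison has 16 per arm, and a MANOVA stands before a primary endpoint that was sized on its own ANOVA

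*Protocol*

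**What the plan says.** Section 4.5 opens by stating that "the overall sample size (N=64) and the size of each group (n=32) are considered sufficient for applying such procedures". It then describes two analyses.

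- **CP versus TD.** A MANOVA on seven named variables: step width, sternum deceleration, L5 deceleration, anterior foot position, ECAB, GMFM-66-IS and the Reaching Hand questionnaire.
- **Rehabilitation effect, PC1 versus PC2.** This "will be tested using the same type of multivariate procedures (MANOVA", in a mixed design with two groups and four visits (M0, M3, M6, M12). No variable list is given for this analysis. The group difference in sternum deceleration at M3, which is the primary question, is a post-hoc comparison made only if the Group × Period interaction is significant.

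Section 3.2.3 describes the sizing differently: "To demonstrate an effect of RAIT using a repeated measures ANOVA", for which "a total sample size of 24 patients, i.e., 12 per group, is necessary". It continues: "we plan to recruit 32 children with CP (16 per group), to account for this greater variability and to compensate for potential dropouts". Section 3.3 adds 32 matched TD children, and section 3.4 has them assessed at M0 only.

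**The concern.** The figures offered in support of the models belong to the comparison that does not carry the primary objective. TD children are not randomised and have no visit after M0, so they contribute nothing to the two-group, four-visit analysis.

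The decision rule also departs from the sizing. The trial was sized for one variable in a repeated measures ANOVA, but the route to the primary claim runs through a multivariate interaction test. If that test pools variables, a real effect on the sternum can be diluted and never reach the M3 contrast. Conversely, a significant omnibus result may come from another variable. The only list in section 4.5 includes Reaching Hand, which section 2.4 does not declare as an endpoint. It omits four of the nine secondary endpoints that section 2.4 does declare: eGVI, the two standing variables and the Edinburgh score.

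**Working it through.** **Inputs.** From section 3.2.3: CP mean 3.0 and SD 1.1 m/s², planned reduction of one third (3.0/3 = 1.0 m/s²), alpha 0.05, 24 children necessary, 32 recruited. From section 4.5: two groups, four visits, seven variables (first-phase list). Assumed, because the documents give no figure: correlation between visits ρ = 0.5 (range 0.3 to 0.7), sphericity, and independence between variables.

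**1. The plan's own figure.** For the interaction in a repeated measures ANOVA, λ = f²·N·m/(1−ρ), with df 3 and 3(N−2). With f = 0.25, m = 4, ρ = 0.5 and N = 24, λ = 0.0625 × 24 × 4/0.5 = 12, df are (3, 66) and power is 0.816. The smallest even N reaching 80% is 24, so the stated number is reproduced for a univariate test. (With f = 0.10, the conventional value for a small effect, N would be 138. That is a separate point.)

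**2. Which N applies where.** CP versus TD on seven variables: N = 64, F df (7, 64−2−7+1) = (7, 56), which is adequate. PC1 versus PC2: N = 32, 16 per arm.

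**3. Planned effect as f.** Suppose the arms differ by 1.0 at M3 only, since PC1 starts RAIT at M3. The differences by visit are 0, 1, 0, 0, with mean 0.25. The squared deviations sum to 3 × 0.0625 + 0.5625 = 0.75. Each arm carries half of each deviation, so the interaction variance is 0.25 × 0.75/4 = 0.0469, with root 0.2165. Then f = 0.2165/1.1 = 0.197. At ρ = 0.5, λ = 0.0387 × 32 × 4/0.5 = 9.92 for N = 32 and 7.44 for N = 24.

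**4. Doubly multivariate interaction test.** Contrasts: 7 × 3 = 21. F df: (21, N−2−21+1) = (21, N−22). This gives (21, 10) at N = 32, (21, 4) at 26, (21, 2) at 24 (critical F 19.45), and no test at 22 or fewer. If k independent variables each move by the planned effect, the noncentrality is kλ.

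**5. Averaged mixed-design MANOVA.** Error df are 3(N−2): 90 at N = 32 and 66 at N = 24, so there is no shortage. Power was simulated with Pillai's trace, seven independent variables and only the sternum moving.

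| Test, ρ = 0.5 | N = 32 | N = 24 |
| --- | --- | --- |
| Univariate repeated measures ANOVA, sternum | 74% | 59% |
| Sternum alone, multivariate over visits (3 contrasts) | 69% | 53% |
| Averaged MANOVA, only sternum moves | about 31% | about 22% |
| Doubly multivariate, only sternum moves | 15% | 7% |
| Doubly multivariate, three variables move | 44% | 10% |
| Doubly multivariate, seven variables move | 85% | 16% |

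Repeated simulation runs gave 31–32% and 21–22% for the averaged form.

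**6. Range over ρ.** For ρ = 0.3, 0.5 and 0.7 at N = 32, the univariate ANOVA has 58%, 74% and 93% power, and the doubly multivariate test with one mover has 12%, 15% and 24%. The ordering does not change.

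**The case against.** The strongest reply is that section 4.5 does not say that seven variables enter the rehabilitation analysis. The list belongs to the CP–TD phase, the second analysis is also called a mixed design, and the only variable named in its M3 comparison is sternum deceleration. Run for the sternum alone, even in multivariate form over visits, the test has 69% and 53% power, close to the univariate ANOVA. This stands: the power loss depends on the reading. But no other list is given, and a MANOVA of the same type naturally suggests the same variables. The wrong N and the gate remain on any reading.

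Second, section 4.4 expects RAIT to improve all seven variables. If all moved equally and independently, even the doubly multivariate test would have 85% power at N = 32. That also stands, under favourable assumptions. It does not help the primary claim, because a test that succeeds through other variables is not evidence about the sternum.

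Three stronger readings may tempt a reader, and the documents do not support them:

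- *The test has almost no error degrees of freedom.* At the planned 32 complete children, 10 denominator df remain. The description fits only the doubly multivariate form at about 26 completers or fewer.
- *A null result is practically certain.* The 44% and 85% above contradict this.
- *Children with any missing visit will be dropped.* Classical MANOVA software often does so, but section 4.5 is silent, and missing-data rules may sit in a statistical analysis plan that is not shown. Section 4.6 says of early stopping that "the final assessment will be performed at the time of study discontinuation, if possible", which does not exclude such data.

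**Conclusion.** The point holds in limited form. It is certain from the text that N=64 and n=32 do not describe the randomised comparison, that this comparison has 16 per arm with the dropout allowance already included, and that the primary contrast is gated by a test other than the one used for sizing.

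The size of the harm is conditional. If the seven listed variables enter and only the sternum responds, power falls from 74% to about 31% (averaged form) or 15% (doubly multivariate form) with 32 complete children, and from 59% to about 22% or 7% with 24. These figures assume a difference at M3 only, SD 1.1, ρ = 0.5 and independent variables. Correlation between variables, or several responding together, would change them. Because this test decides whether the primary contrast is examined at all, it should be settled before analysis.

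**What to change.** - In section 4.5, keep N=64 and n=32 for the CP–TD comparison only, and state N=32 with 16 per arm for PC1 versus PC2.
- Test the primary endpoint in its own baseline-adjusted repeated-measures model, for example a mixed model with group, visit and their interaction that uses all available visits. Name the M3 group contrast as the primary test, not conditional on a multivariate result. This brings the analysis back to the single endpoint on which the trial was sized.
- Analyse the nine secondary endpoints of section 2.4 in separate secondary models, with Reaching Hand labelled exploratory.

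The cost is protocol wording, slightly more modelling work and the loss of one omnibus p-value across variables. No extra children or visits are needed.

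### The regression of anterior foot load on trunk decelerations, placed in the CP-versus-TD phase, lists no CP/TD term and does not say which children enter it; if the groups are pooled, the expected CP/TD gap can by itself produce a significant association

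*Protocol*

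**What the plan says.** Protocol 4.5 opens by justifying general linear models, "as the overall sample size (N=64) and the size of each group (n=32) are considered sufficient". The next paragraph begins "In the first phase, the group effect (Children with CP vs. TD Children) will be analyzed" and sets out a MANOVA. The same paragraph then adds a multiple linear regression, "with the anterior foot position during the 1st double-support phase as the dependent variable and the sternum and L5 decelerations" early in stance as the regressors. Nothing else is listed: no CP/TD term, no restriction to one group, no separate fits. The two randomised CP groups appear only in the paragraph after that.

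On the variables themselves, Protocol 4.4 expects, in children with CP compared with TD children, higher sternum and L5 decelerations and "A greater anterior foot load during the 1st double-support phase". Section 4.3.2 says why foot load should differ: forefoot contact in CP, heel contact in TD. Section 4.5 speaks of anterior foot position where 2.4 and 4.3.2 speak of anterior foot load; I take these to be the same variable.

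For the sternum, 3.2.3 reports that in the previous study "this distribution was centered on 3.0 ± 1.1 m.s-2 (mean ± 1 standard deviation) in children with CP" and "on 1.1 ± 0.3 m.s-2 in TD children". The protocol gives no comparable figures for L5 or for foot load.

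**The concern.** Group membership is expected to shift the outcome and both regressors in the same direction, and it is left out of the model. In a pooled fit, any CP/TD difference in foot load is then partly credited to the decelerations. A significant result could mean that children with greater trunk deceleration load the forefoot more. It could equally mean only that children with CP differ from TD children on each variable separately, which the MANOVA in the same paragraph already tests.

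This is the only analysis in 4.5 that relates trunk deceleration to foot loading. A reader would naturally set its result beside the argument in section 1 that the plantar flexors compensate for poor trunk control. A pooled fit without a group term cannot tell the two explanations apart.

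**Working it through.** **Plan's own figure.** The protocol gives no effect size, power or expected result for this regression, so there is none to reproduce.

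**Inputs from the protocol.** 32 CP and 32 TD children (4.5); sternum deceleration 3.0 ± 1.1 and 1.1 ± 0.3 m.s-2 (3.2.3, from the previous study at ages 5 to 12).

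**Assumptions.** Test level 0.05 (stated in 3.2.3 for the sample size only); L5 gap 0.8 or 1.5 SD; within-group correlation of sternum and L5 either 0 or 0.5; foot-load gap from 0 to 2.0 SD; no association between foot load and either deceleration within CP or within TD.

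**Step 1: how strongly group drives the sternum regressor.** With equal groups:
- gap = 3.0 − 1.1 = 1.9, so between-group variance = (1.9/2)² = 0.9025
- average within-group variance = (1.1² + 0.3²)/2 = (1.21 + 0.09)/2 = 0.65
- between-group share = 0.9025/(0.9025 + 0.65) = 0.58
- correlation of group with sternum deceleration = √0.58 = 0.76
- standardised gap = 1.9/√0.65 = 2.36 SD

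**Step 2: correlation created by pooling alone.** With no within-group link, the pooled sternum–foot-load correlation is the product of each variable's correlation with group. For a foot-load gap of d SD, the latter is (d/2)/√((d/2)² + 1).
- d = 0.5: 0.25/√1.0625 = 0.243; × 0.762 = 0.19
- d = 1.0: 0.5/√1.25 = 0.447; × 0.762 = 0.34
- d = 1.5: 0.75/√1.5625 = 0.600; × 0.762 = 0.46

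The simulation below gives the same three values.

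**Step 3: false-positive rate.** 2,000 simulated data sets per scenario. Ranges run over the L5 gap (0.8, 1.5 SD) and the sternum–L5 correlation (0, 0.5). The joint test is the F-test of both decelerations.

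| Foot-load gap (SD) | Pooled, no group term: joint test | Sternum coefficient alone |
| --- | --- | --- |
| 0 | about 5% | about 5% |
| 0.5 | 24-27% | 16-26% |
| 0.8 | 54-61% | 32-55% |
| 1.0 | 73-79% | 44-73% |
| 1.5 | 97-99% | 73-96% |
| 2.0 | about 100% | 88-99% |

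The L5 coefficient alone is much less affected: 4-9% at a foot-load gap of 0.5 SD and 6-49% at 2.0 SD.

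**Step 4: the same data, group handled.** Over all scenarios the joint test rejects in 3.8-5.8% with a CP/TD term added, and in 3.9-6.0% when fitted in the 32 children with CP only.

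**Step 5: sensitivity.**
- If L5 separates the groups as strongly as the sternum (about 2.4 SD), the rate at a 1 SD foot-load gap lies at or above the top of the range in the table, up to about 86%.
- Section 3.2.3 expects greater variability at 18 months to 5.5 years. If the SDs are 1.5 times larger for the same mean gap, the between-group share falls to 0.9025/(0.9025 + 2.25 × 0.65) = 0.9025/2.365 = 0.38, and the rate at a 1 SD foot-load gap is about 52-76%, depending on L5.

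**The case against.** Pooling is inferred, not stated. Section 4.5 names an outcome and two regressors but no sample; a fit confined to children with CP would have no such problem, and which children enter an ancillary model is often left to a statistical analysis plan. This stands in part. The silence about the sample alone would not be worth raising. But the protocol does fix the regressor list, in a paragraph about comparing CP with TD and under a justification that cites all 64 children. Followed as written, that specification is confounded by group.

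The inputs are also soft, and this stands. The foot-load measure was developed for this study and its CP/TD gap is given nowhere; there are no L5 figures; the sternum figures come from older children.

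A pooled regression can further be defended as describing a marginal association across all children. That is legitimate if it is labelled so, but it is not evidence of a link within children with CP.

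Two stronger readings are tempting. A reader might infer that the regression is bound to come out significant whatever the truth. The figures do not support that: at a foot-load gap of 0.5 SD it happens in about one trial in four. A reader might also infer that the trial's mechanistic rationale rests on this regression. The protocol gives it no such role: no objective, endpoint or expected result concerns an association, and section 1 argues the rationale from the earlier study. Nor does the argument call for an age term, since 3.3 matches the TD children on age and sex.

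**Conclusion.** The point holds in a limited form. The regression specified in 4.5 has no CP/TD term and no stated sample. If the 64 children are pooled, which is the natural reading, the group differences that the protocol itself expects can generate a significant association where none exists within either group. The inflation is about fivefold at an assumed foot-load gap of 0.5 SD (24-27% against 5%), reaches 73-79% at 1 SD, and is near certainty only from about 1.5 SD. These rates rest on the sternum figures for ages 5 to 12 and on assumed L5 and foot-load gaps; larger SDs in the younger children would lower them. It is the joint test and the sternum coefficient that are mainly affected, the L5 coefficient less so.

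The analysis is ancillary. The primary endpoint, the sample size, the randomisation and the comparison of the two rehabilitation programmes do not depend on it.

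**What to change.** Add one sentence to 4.5 stating that the regression is fitted in the children with CP, or is fitted in both groups with a CP/TD term, and that only the within-group coefficients will be read as evidence of a link between trunk deceleration and foot loading. If a pooled marginal association is also wanted, label it descriptive.

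The cost is small and no new data are needed. A group term takes one residual degree of freedom (64 − 4 = 60 instead of 64 − 3 = 61). A CP-only fit leaves 32 − 3 = 29, so it is less precise, but it addresses children with CP directly.

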**3.4. Experimental Plan**

The project includes a clinical examination and instrumental functional explorations at four time points. The experimental plan is shown in Figure 4. The assessments are described in chapter "4.3. Measurements – Description of assessments performed during the research." Assessments will be conducted at M0, M3 (M0 + 3 months), M6 (M0 + 6 months), and M12 (M0 + 12 months) for children with CP and at M0 for TD children. Thus, three rehabilitation periods will be planned: the first between M0 and M3, the second between M3 and M6, and the third between M6 and M12. A first group of children (group PC1) will continue their usual rehabilitation (RH) for the first 3 months and then will have RAIT for the following 9 months (PC1 = RH-RAIT). The second group of children, PC2, will immediately have RAIT for the 12 months of the study (PC2 = RAIT-RAIT). As the previous study conducted in children with CP aged 5 to 12 years showed a therapeutic effect only related to RAIT (and not to RH), RAIT will be continued for the children who benefited from it from the first 3-month period and for all children for the last 9 months of the study. Such a plan will allow to: 1) ensure that all children with CP benefit from RAIT; 2) measure the effect of RAIT over 3 months compared to that of RH; 3) test the reproducibility of the effect of RAIT over 3 months between the two groups and 4) test the effect of an additional 3 months of RAIT in the PC2 group (M6 versus M3) and 6 months in both groups (M12 versus M6) (**Figure 4**).

[figure not shown]

**Figure 4:** Experimental plan of the study. RAIT: rehabilitation through postural activities involving the trunk; conventional rehabilitation is based on the treatment of muscle groups (stretching, strengthening, tone reduction) of the lower limbs

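### The Tukey tests named for reproducibility of the RAIT effect never compare the two 3-month changes, and a test of difference cannot show that they are similar

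*Protocol*

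**What the plan says.** Section 3.4 lists four things that the design will allow. The third is to "test the reproducibility of the effect of RAIT over 3 months between the two groups". PC1 (RH-RAIT) starts RAIT at M3 and PC2 (RAIT-RAIT) starts at M0, so each group has a first 3-month RAIT period.

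Section 4.5 gives the method. If the Group × Period interaction in the 2 × 4 mixed design is significant, "the analysis of local comparisons using post-hoc procedures (Tukey's tests) will allow us to examine" three items. The second is "the reproducibility of the RAIT effect (similar differences between M3 and M6 for the RH-RAIT group and between M0 and M3 for the RAIT-RAIT group". The Protocol does not say what counts as similar.

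The sample size in section 3.2.3 does not refer to this aim. It is derived "using a repeated measures ANOVA in which we expect a small effect size".

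**The concern.** The tool named does not answer the question set, for two reasons.

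1. Tukey's procedure compares pairs of means. With 2 groups and 4 visits there are 8 means and 8 × 7 / 2 = 28 pairs. The quantity of interest, (M6−M3 in PC1) minus (M3−M0 in PC2), uses four means and is none of those pairs.
2. Similarity is a claim that no important difference exists. Tukey tests look for differences, and failing to find one in a small trial says little.

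An analyst would therefore have to improvise. One route is to test the difference of the two changes and read non-significance as similar (reading A). The other is to ask whether both within-group Tukey tests are significant (reading B). The two routes err in opposite directions, and nothing in the Protocol chooses between them. At stake is an unsupported statement, either way, about one of the four stated purposes of the design.

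**Working it through.** **Inputs from section 3.2.3.** The primary endpoint in CP is "centered on 3.0 ± 1.1 m.s-2 (mean ± 1 standard deviation) in children with CP". The expected RAIT reduction is one-third of 3.0, which is 1.0 m.s-2, so a half-sized effect is 0.5. The plan is 16 per group.

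**Assumptions.** No dropout, two-sided 5% tests, equal correlation r between visits, effects that persist once reached, and a univariate 2 × 4 mixed ANOVA as the interaction gate. Mean profiles are PC2 = 3, 2, 2, 2 and PC1 = 3, 3, 3−d, 3−d, with d = 1.0 (identical effect), 0.5 (half) or 0 (none). The text gives no value of r.

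**The plan's own figure.** The Protocol states that "a total sample size of 24 patients, i.e., 12 per group, is necessary". For the within-between interaction with 2 groups and 4 visits, λ = f² × N × m / (1−r). With f = 0.25 and r = 0.5, λ = 0.0625 × 24 × 4 / 0.5 = 12, and power is 0.816 at N = 24. So r = 0.5 is compatible with the stated size, though Figure 3 is not available to confirm it. The range 0.3 to 0.9 is therefore shown.

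**Precision of the needed contrast.** SD of a change = 1.1 × √(2(1−r)). SE of the contrast = SD of change × √(2/16). The 95% half-width uses t(30) = 2.042.

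| r | SD of change | SE | 95% half-width |
|---|---|---|---|
| 0.3 | 1.30 | 0.46 | 0.94 |
| 0.5 | 1.10 | 0.39 | 0.79 |
| 0.7 | 0.85 | 0.30 | 0.62 |

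**Reading A: non-significant difference of changes.** For a half-sized effect in PC1 the true contrast is 0.5, so the noncentrality is 0.5/SE = 1.09 / 1.29 / 1.66. The noncentral t gives non-significance in 82 / 76 / 64% of trials before any gate. Simulation with the gate gives:

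| r | Half effect called similar, given a significant interaction | Same, as a share of all trials |
|---|---|---|
| 0.3 | 74% | 30% |
| 0.5 | 70% | 38% |
| 0.7 | 60% | 48% |

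Given the gate, the figure falls to about 48% at r = 0.8 and 21% at r = 0.9. Section 3.2.3 expects more variability than in the older children. With an illustrative SD of 1.4, the ungated 76% at r = 0.5 becomes 84%; with 12 per group at SD 1.1 it becomes 81%.

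**Reading B: both within-group Tukey tests significant.** The family is 8 means with 90 error df (30 × 3). By simulation, a single test of a true change of 1.0 has power of about 49 / 70 / 94%, and of a true change of 0.5 about 6 / 10 / 24%. The two groups are nearly independent, so the products are close to the simulated joint results. For identical effects they are 0.49² = 0.24, 0.70² = 0.49 and 0.94² = 0.88.

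| r | Identical effects confirmed, all trials | Same, given the gate | Half effect passes, all trials | Same, given the gate |
|---|---|---|---|---|
| 0.3 | 25% | 40% | 3% | 8% |
| 0.5 | 49% | 62% | 8% | 13% |
| 0.7 | 89% | 92% | 22% | 27% |

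Reading B also depends on the Tukey family, which is not stated. At r = 0.5, given the gate, a half-sized effect passes in 13% with 8 means and 29% with 4.

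**The case against.** The strongest reply is that no decision rule exists to be criticised. Section 4.5 says the comparisons allow reproducibility to be examined. It attaches no success claim, and a definition of similar could sit in a statistical analysis plan that is not shown. Reproducibility is also absent from the primary objective (section 2.1) and from the three secondary objectives (section 2.3).

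Most of this stands, and it limits how much can be said. A reader might infer that a half-sized effect in PC1 would usually be called reproduced. The Protocol does not support that. It is true only under reading A, whose test section 4.5 never mentions, and only at correlations below about 0.8. Counting all trials, including those stopped at the interaction gate, it happens in 30 / 38 / 48%. Under reading B, which is closer to the named tool, a half-sized effect passes in only 3 / 8 / 22%.

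A reader might also infer that an absent second effect would be confirmed. With the gate, that occurs in about 19 / 17 / 9% of all trials under reading A and about 0.1% under reading B.

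The reply does not remove the mismatch. This is more than detail left for later: the Protocol itself names both the procedure and the target, and the procedure does not estimate the target.

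**Conclusion.** The point holds as a minor one about method. Tukey comparisons of cell means do not compare the two 3-month changes, and tests of difference cannot support a statement of similarity.

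The direction of the error depends on the unstated rule. Reading A is lenient towards an effect that is only half reproduced. Reading B often denies an effect that is fully reproduced, at least for correlations up to about 0.5. All percentages rest on the Protocol's SD and effect, 16 completers per group and an assumed correlation. The gate was modelled as univariate, although section 4.5 describes a MANOVA.

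The between-group comparison at M3, which carries the primary objective, is not affected.

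**What to change.** - In section 4.5, replace item 2 by one prespecified contrast from the repeated-measures model, (M6−M3 in PC1) minus (M3−M0 in PC2). Report it as an estimate with its 95% CI whether or not the interaction is significant.
- State there that a non-significant contrast, or Tukey p-values that match or differ between groups, will not be read as evidence for or against reproducibility.
- In section 3.4, change test to estimate for the third aim.

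A formal equivalence margin is not recommended. With an illustrative margin of 0.5 m.s-2, 5% per side and 80% power, about 83 children per group would be needed at r = 0.5.

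The cost is a few lines of text and one model contrast, with no extra children or visits. The downside is a more modest claim: the interval would probably extend 0.6 to 0.9 m.s-2 either side of the estimate, against an expected effect of 1.0.
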